### **11.5 Decision rule**

A decision rule will be implemented following the calculation of the failure rate and confidence limits to decide whether the treatment should be warrant for a future comparative trial. A 30% increasing in the median time of survival (or 26% reduction in the failure rate) compared to NABTT historical data would be considered strong evidence in favor of proceeding with a formal comparative trial. Less than 30% improvement in the median time of survival or less than 26% reduction in the failure rate compared to the historical data would be considered neither reliable nor promising enough clinically to pursue a randomized trial. However, these decision rules ultimately are partially subjective and depend greatly on the toxicities associated with the treatment.

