### **11.2 Primary Objective**

To estimate an overall survival, the primary objective of the study is to estimate the overall failure rate compared to the failure rate of the NABTT historical phase II clinical trial database in the same patient population. There are 62 GBM patients who participated in three closed NABTT phase II clinical trials and were treated with single or combination of experimental chemotherapies (protocol number: 9502, 9506, 9706, 9711, and 2111). The estimated historical hazard rate is 1.67 per person-year of follow-up (95% CI: 1.3, 2.14) and an estimated historical median time of survival is 5 months.

The primary endpoint is death. The survival time is defined from time of first day of the treatment to death occurrence. The overall failure rate is expressed as hazard of failure per person-year of follow-up (the number of deaths divided by the total exposure time in the study cohort). The total patient population of this study is defined as all patients who have met eligibility criteria, not met ineligibility criteria and signed informed consent, which will be included in the statistical estimations.

To estimate the overall failure rate with sufficient precision, a total of 52 events are required from 56 patients at an accrual rate of 4 patients per month for 14 months, and with 1.5 years of additional follow-up (total study duration is 2.7 years). We assume that patients in the study will have an overall failure rate of 1.25 per person-year of follow-up, about 25% reduction compared to a hazard rate of 1.67 shown in the relevant NABTT historical database. The 52 events among the 56 patients during the planned follow-up will yield 80% power to detect an observed hazard ratio of 0.75 (1.25 vs. 1.67) to be statistically significant at an alpha level of 0.1 (one-side, A Methodologic Perspective, Piantadosi 1997). The 25% reduction in hazard rate translates into a 33% increase in median time of survival (from 5 month to 6.65 month). Moreover, the total of 52 events will yield 90% power to detect a 30% reduction in observed hazard ratio of 0.7 (1.17 vs 1.67) to be statistically significant, which increases the median time of survival in 40% (from 5 month to 7 month).

The overall failure rate will be estimated along with 95% confidence intervals. A median time of survival will be estimated using standard methods.

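### The go/no-go threshold in 11.5 pairs a 30% longer median with a 26% lower failure rate, which do not match under the protocol's own conversion, and no measure is named as governing

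*Protocol*

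**What the plan says.** Section 11.2 makes the failure rate the primary measure and defines it as "the number of deaths divided by the total exposure time in the study cohort". For the comparator it says: "The estimated historical hazard rate is 1.67 per person-year of follow-up (95% CI: 1.3, 2.14) and an estimated historical median time of survival is 5" (in months). Planning assumes a rate of 1.25 per person-year, and 11.2 converts this to the median scale: "The 25% reduction in hazard rate translates into a 33% increase in median time of survival", from 5 to 6.65 months.

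Section 11.5 then gives the rule for going on to a comparative trial. The favourable result is "A 30% increasing in the median time of survival (or 26% reduction in the failure rate) compared to NABTT historical data", which "would be considered strong evidence in favor of proceeding with a formal comparative trial". The unfavourable result is "Less than 30% improvement in the median time of survival or less than 26% reduction in the failure rate compared to the historical data", which "would be considered neither reliable nor promising enough clinically to pursue a randomized trial". The section closes by saying that "these decision rules ultimately are partially subjective and depend greatly on the toxicities associated with the treatment". It does not say which of the two measures decides if they disagree.

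**The concern.** Under a constant hazard, the median and the failure rate carry the same information, and a threshold on one fixes the threshold on the other. The pair in 11.5 does not follow the relation that 11.2 uses.

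The 'or' adds to this. In the go sentence, meeting either figure is enough. In the no-go sentence, missing either figure is enough. Any result that meets one figure and misses the other therefore receives both labels.

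At stake is the recommendation that the trial exists to inform. If the ambiguity is settled only once the estimate is known, the choice of criterion can follow the data.

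**Working it through.** **Inputs.** From 11.2: historical rate 1.67 per person-year; historical median 5 months; planned rate 1.25; 52 deaths among 56 patients; one-sided alpha 0.10; 14 months of accrual plus 1.5 years of follow-up. From 11.5: 30% on the median, 26% on the rate.

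**Step 1: reproduce the plan's own figures.** With a constant hazard, median = ln 2 / rate, so the ratio of medians is 1/HR.
- 12 × ln 2 / 1.67 = 4.98 months (plan: 5).
- 12 × ln 2 / 1.25 = 6.65 months (plan: 6.65).
- 1/0.75 = 1.333, a 33% longer median (plan: 33%).
- Power against a fixed historical rate, Φ(√52 × |ln HR| − 1.282): 78.6% at HR 0.75 (plan: 80%) and 90.2% at HR 0.70 (plan: 90%).

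So 11.2 uses the exponential model, with the historical rate treated as known.

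**Step 2: convert the 11.5 thresholds in the same way.**

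| Threshold stated | HR | Rate per person-year | Equivalent on the other scale | Median |
|---|---|---|---|---|
| Median +30% | 1/1.30 = 0.769 | 1.67/1.30 = 1.285 | rate −23.1% | 5 × 1.30 = 6.5 months |
| Rate −26% | 0.740 | 1.67 × 0.74 = 1.236 | median +35.1% (1/0.74 = 1.351) | 5/0.74 = 6.76 months |

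The figures do not match. Results with HR between 0.740 and 0.769 meet the median figure and miss the rate figure.

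**Step 3: place the design effect.** A rate of 1.25 lies between 1.236 and 1.285. It is about a 25% reduction and a 33% longer median, so it meets 30% and misses 26%. A trial that observed exactly what it was planned for would carry both labels.

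**Step 4: size of the zone.** Take the observed log rate as normal with SE = 1/√52 = 0.139, and derive the median from the rate.
- True HR 0.75, go at the 30%-median equivalent: Φ((ln 0.769 − ln 0.75)/0.139) = 57.2%.
- True HR 0.75, go at a 26% reduction: Φ((ln 0.740 − ln 0.75)/0.139) = 46.1%.
- Chance of landing between them: 57.2% − 46.1% = 11.1%.
- True HR 0.70: 75.2% − 65.6% = 9.6%.
- True HR 1.0: 2.9% − 1.5% = 1.4%.

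**Step 5: if both measures are estimated from the data.** Simulation: 20,000 trials per setting, 56 patients, uniform accrual, exponential survival, Kaplan-Meier median, rate as deaths over person-years. Share of trials in which the two criteria disagree:

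| Pair of thresholds | HR 0.75 | HR 0.70 |
|---|---|---|
| 30% / 26%, as written | 25.1% | 23.1% |
| 30% / 23.1%, matched | 24.9% | 23.1% |
| 35.1% / 26%, matched | 24.3% | 24.8% |

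Matching the thresholds leaves the disagreement essentially unchanged.

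**The case against.** **The parenthesis is a restatement.** The 26% reads naturally as the same threshold on another scale, not as a second route to a go. Section 11.5 opens by tying the rule to the calculated failure rate and its confidence limits, and 11.2 makes that rate primary, so a reader could infer that the rate leads. This stands in part: the likely origin is a conversion slip. But the protocol never says that the rate governs, and the no-go sentence again names both figures.

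**The rule is advisory.** Section 11.5 calls it partly subjective and dependent on toxicity. It does not touch the primary estimate, its 95% interval, the sample size or the significance test. The zone is also narrow: exp(1.96 × 0.139) = 1.31, so the observed rate is known only to within a factor of about 1.3. This stands and limits the severity. It does not reconcile the two numbers or say which one decides.

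**Survival may not be exponential.** Then no fixed pairing exists and two unranked criteria can still conflict. Section 11.2 uses the exponential model in any case.

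**A stronger reading to avoid.** A reader might infer that the mismatch makes the rule contradict itself in about a quarter of trials. Step 5 does not support that. That disagreement is sampling noise between two estimators and remains with matched thresholds. It is a separate reason to name one governing measure.

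**Conclusion.** The point holds. Section 11.5 states a mis-converted threshold and names no governing measure. Read literally, it gives both verdicts to any result with HR between 0.740 and 0.769, and that zone contains the planning effect.

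The part attributable to the mismatch is about an 11% chance of landing in the zone at a true HR of 0.75 and about 10% at 0.70. Which cut-off governs moves the chance of a go at 0.75 between 57% and 46%. These figures assume 52 deaths, exponential survival, a historical rate fixed at 1.67 and a median derived from the rate.

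This should be fixed, but it is not a condition for a valid trial. A reader might infer that the error undermines the primary analysis or the stated power. It does not: the estimate and its interval do not depend on 11.5, and the power figures in 11.2 reproduce to within two percentage points.

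**What to change.** Amend 11.5 before results are known:

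1. Make the failure rate, the primary measure in 11.2, the only decision criterion.
2. State one threshold, with the converted median beside it as description only. Either a 23% reduction (rate at most 1.285, 30% longer median, 6.5 months) or a 26% reduction (rate at most 1.236, 35% longer median, about 6.8 months).
3. Delete the 'or' in both the go and the no-go sentence.
4. Report the probability of a go that the chosen threshold implies. The 80% power in 11.2 refers to statistical significance and is not that probability.

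Correcting the number while keeping two estimated criteria would not be enough, because they would still disagree in roughly a quarter of trials.

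The text change is small, and sample size and follow-up stay as they are. The real cost is that the sponsor must choose between the two cut-offs, which moves the go probability at HR 0.75 by about 11 percentage points.

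### The go/no-go rule in section 11.5 contradicts itself at the design effect, and the 80%/90% power in section 11.2 does not describe that rule

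*Protocol*

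**What the plan says.** Section 11.2 of the protocol sizes the trial against a historical benchmark: "The estimated historical hazard rate is 1.67 per person-year of follow-up (95% CI: 1.3, 2.14"), with a historical median of 5 months. It assumes an "overall failure rate of 1.25 per person-year of follow-up, about 25% reduction compared to a hazard rate of 1.67", which it converts to a 33% longer median (5 to 6.65 months). For this "a total of 52 events are required from 56 patients at an accrual rate of 4 patients per month for 14 months", followed by 1.5 further years of follow-up. It states that these events "will yield 80% power to detect an observed hazard ratio of 0.75 (1.25 vs. 1.67) to be statistically significant" at a one-sided alpha of 0.1, with 90% power at a hazard ratio of 0.70.

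Section 11.5 governs what is done with the result. The go sentence treats a 30% longer median, or in brackets a 26% lower failure rate, as strong evidence for a comparative trial. The no-go sentence says that "Less than 30% improvement in the median time of survival or less than 26% reduction in the failure rate compared to the historical data" would not justify one. The section adds that the rule is partly a matter of judgement and depends heavily on toxicity.

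**The concern.** Two things do not fit together.

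First, section 11.5 offers a median figure and a rate figure as interchangeable, but under the model in section 11.2 they are different thresholds. Both sentences join them with *or*, so a result that passes one and fails the other is both a go and a no-go. The effect for which the trial is sized is such a result.

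Second, the only performance figures in the protocol are the 80% and 90% power of a significance test. Section 11.5 does not apply that test; both of its thresholds ask for a much larger observed effect. A sponsor or monitoring committee reading section 11.2 could expect a drug with the targeted benefit to go forward about four times in five, and section 11.5 does not deliver that. Whether to run a comparative trial is the stated use of the primary result, so the rule should give one answer and its properties should be known.

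**Working it through.** **Inputs.** From section 11.2: 52 deaths, 56 patients, 14 months of accrual, 1.5 years of further follow-up, historical rate 1.67 per person-year, design rate 1.25, one-sided alpha 0.10. From section 11.5: 30% longer median, 26% lower rate. Survival is taken as exponential and 1.67 as a fixed reference, as section 11.2 does.

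**1. The stated power reproduces.** Power = Φ(√52 × |ln HR| − 1.2816), with √52 = 7.211.
- HR 0.75: 7.211 × 0.2877 − 1.2816 = 0.793, so 78.6% (79.1% by the exact chi-square calculation). Stated: 80%.
- HR 0.70: 7.211 × 0.3567 − 1.2816 = 1.290, so 90.2%. Stated: 90%.

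The test is met at an observed HR of exp(−1.2816/7.211) = 0.837 or lower. That is a reduction of about 16%, or an observed rate of 0.837 × 1.67 = 1.40.

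**2. The two criteria in section 11.5 are different thresholds.** With exponential survival the median is ln 2 divided by the rate: 0.693/1.67 × 12 = 4.98 months, the stated 5. The ratio of medians is then 1/HR, which also gives the protocol's own 33% (1/0.75 = 1.333).
- 30% longer median: HR = 1/1.30 = 0.769, a 23.1% lower rate (1.67/1.30 = 1.285).
- 26% lower rate: HR = 0.74, a 35.1% longer median (1/0.74 = 1.351; rate 0.74 × 1.67 = 1.236).

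Observed rates between 1.236 and 1.285 pass the median criterion and fail the rate criterion. The design rate of 1.25 lies inside that band.

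**3. Chance of a go when each criterion is applied mechanically.** P(go) = Φ(√52 × ln(c/HR)), where c is the cut-off for the observed HR.

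| True HR | 26% rate (c = 0.74) | 30% median (c = 0.769) | Significance test in 11.2 |
|---|---|---|---|
| 0.75 | 46% | 57% | 79% (stated 80%) |
| 0.70 | 66% | 75% | 90% (stated 90%) |
| 1.00 | 1.5% | 2.9% | 10% (the stated alpha) |

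For example, at HR 0.75 on the rate criterion: 7.211 × ln(0.74/0.75) = −0.097, so Φ = 0.461. Exact chi-square values at HR 0.75 are 44% and 55%.

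**4. Other readings.** The planned accrual and follow-up were simulated at a true rate of 1.25, which gave about 51.5 deaths on average. The rate criterion gave 45%. Requiring an observed median of at least 6.5 months (5 × 1.30), read from the ordered survival times, gave 49%. Requiring both criteria gave 35%, and accepting either gave 60%. The gap between either and both (60 − 35) means that the two criteria disagree in about one trial in four at the design effect.

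**5. Effect needed for an 80% chance of a go.** The true HR would have to be about 0.66 on the rate criterion or 0.68 on the median criterion, against the planned 0.75.

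**The case against.** The power statement in section 11.2 is not an error. It claims 80% for statistical significance at one-sided 0.10, and that reproduces. The protocol nowhere promises an 80% chance of a go, nor states a false-go rate; the 10% is the alpha of the test. This stands.

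Asking for more than significance before a randomized trial is a legitimate clinical choice. Any cut-off placed at the design effect gives a go chance near 50%, and the step from 25% to 26% costs only about four points. This also stands: the low go chance follows mainly from where the threshold sits, not from that one-point gap.

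The rule is declared partly subjective and dependent on toxicity, so percentages from mechanical use are not forecasts of what will be decided. True, but judgement does not repair two sentences that classify the same result in opposite ways.

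Three stronger inferences are tempting and are not supported:
- A reader might conclude that the design effect is simply a no-go, or that the 80% is really 46%. Both follow only from the rate criterion. The design effect's 33% longer median passes the 30% criterion.
- A reader might conclude that a drug with the targeted benefit would be dropped more often than advanced. That depends on the reading; the median criterion gives 57% and accepting either gives 60%.
- A reader might take the sentence "The overall failure rate will be estimated along with 95% confidence intervals" as a third hurdle, that the interval must exclude 1.67. Section 11.2 describes estimation, and section 11.5 does not say what the limits must show.

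**Conclusion.** The concern holds as an inconsistency within section 11.5 and between it and section 11.2. The median and rate figures differ by about three points of rate reduction (23.1% against 26%), and an observed result equal to the design effect meets the go and the no-go sentence at once. The 80% and 90% remain correct for the significance test but are not properties of the rule that uses the primary result. On the readings tried, the chance of a go at a true HR of 0.75 is about 35% to 60%. The chance of advancing an ineffective drug is about 1.5% on the rate criterion and 2.9% on the median criterion.

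These figures rest on exponential survival, a historical rate fixed at 1.67, 52 deaths and mechanical use of the thresholds. The conflict between the median and rate figures needs only the exponential conversion that section 11.2 already uses.

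**What to change.** In section 11.5, state one threshold on one scale. If the other scale is shown as well, make it the matching value: for example, a 30% longer median with a 23% lower rate, or a 26% lower rate with a 35% longer median. Word go and no-go as complements so that every result falls under exactly one. Which threshold to keep is the sponsor's choice.

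Then give the chosen rule's operating characteristics beside the power in section 11.2: 46% / 66% / 1.5% at HR 0.75 / 0.70 / 1.0 for the 26% rate threshold, or 57% / 75% / 2.9% for the 30% median threshold read as a rate. If the go decision is to rest on an estimated median rather than the rate, calculate the figures for that estimator. Say that the 80% and 90% apply to the significance test only, and that the final decision also weighs toxicity.

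Using the significance boundary as the go rule would restore the stated power. It would also accept an observed reduction of about 16%, which section 11.5 treats as too small to pursue, so it is a trade-off rather than a correction.

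The cost is wording, and a stated chance of a go that looks less favourable than 80%. Sample size, follow-up and endpoint are unchanged.

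### The 80% and 90% power in Protocol 11.2 belong to a significance test that the go rule in 11.5 does not use; applied as written, that rule passes a drug with the planned effect only about 45% to 56% of the time

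*Protocol*

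**What the plan says.** Protocol 11.2 takes a historical failure rate of 1.67 deaths per person-year (median 5 months) as the comparator. It then sets the planning assumption: "We assume that patients in the study will have an overall failure rate of 1.25 per person-year of follow-up, about 25% reduction". On size it says that "a total of 52 events are required from 56 patients at an accrual rate of 4 patients per month for 14 months". Patients are then followed for a further 18 months. The 52 deaths are said to give "80% power to detect an observed hazard ratio of 0.75 (1.25 vs. 1.67) to be statistically significant" at a one-sided alpha of 0.1, and 90% power at a ratio of 0.70. The same section equates the 25% reduction with a 33% longer median (5 to 6.65 months).

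Protocol 11.5 sets the rule for going on to a comparative trial. Strong evidence in favour is a 30% gain in median survival or, in parentheses, a 26% lower failure rate. On the other side, "less than 26% reduction in the failure rate compared to the historical data would be considered neither reliable nor promising enough clinically". A median gain below 30% is treated in the same way, so either shortfall counts against a randomized trial. The section does not mention the test in 11.2. It closes by saying that the rules are partly subjective and depend greatly on toxicity. Neither section gives a probability of a go.

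**The concern.** The sample size is justified by one criterion (significance against 1.67) and the decision is taken by another (the size of the observed reduction). If the second were no stricter than the first, the stated power would be a fair guide to the decision. It is much stricter. The cut-off on the observed estimate lies at about the true effect that the trial assumes, and an estimate falls on either side of the true value about equally often.

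The decision on a comparative trial is the one use that the protocol makes of the primary endpoint. A reader who takes 80% power and a 10% error rate from 11.2 as properties of that decision is misinformed on both. The chance of advancing a drug with the planned benefit is far lower, and the chance of advancing an inactive drug is also far lower. Many trials could be statistically significant under 11.2 and a no-go under 11.5.

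**Working it through.** **Inputs (Protocol 11.2 and 11.5).** Historical rate 1.67; planned rate 1.25, ratio 1.25/1.67 = 0.7485, about 0.75; second effect 0.70; 52 deaths; one-sided alpha 0.10 (z = 1.2816); 56 patients over 14 months with 18 months of further follow-up. The go cut-offs are an observed reduction of 26% (ratio 0.74) or a median gain of 30%.

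**Model.** Exponential survival against a fixed historical rate, so the standard error of the log rate ratio is 1/√52 = 0.139 (√52 = 7.211).

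**1. The plan's own figures.** Power = Φ(√52 × |ln HR| − 1.2816).
- HR 0.75: 78.6% (exact chi-square 79.1%), against 80% stated.
- HR 0.70: 90.2% (exact 90.0%), against 90% stated.

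Both reproduce. Expected deaths at a rate of 1.25 under the stated accrual and follow-up are 51.5, against 52 stated.

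**2. What significance requires.** Critical observed ratio = exp(−1.2816/7.211) = 0.837. That is a rate of 0.837 × 1.67 = 1.40 per person-year, a 16% reduction.

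**3. What the go rule requires.**
- 26% limb: ratio 0.74, a rate of 0.74 × 1.67 = 1.236. The implied median gain is 1/0.74 − 1 = 35%.
- 30% median limb under the exponential relation: ratio 1/1.3 = 0.769, a reduction of 23.1%, a rate of 1.67/1.3 = 1.285.

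**4. Probability of a go.** P(observed ratio ≤ c) = Φ(√52 × ln(c/HR)). For example, c = 0.74 and HR = 0.75 give Φ(7.211 × (−0.0134)) = Φ(−0.097) = 46.1%. Each cell shows normal approximation / exact chi-square / simulation of the accrual plan.

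| True HR | Go at 26% reduction | Go at 23.1% reduction | Power for significance stated in 11.2 |
|---|---|---|---|
| 0.75 | 46.1 / 44.3 / 45.1% | 57.2 / 55.4 / 56.0% | 80% |
| 0.70 | 65.6 / 63.7 / 64.1% | 75.2 / 73.3 / 73.6% | 90% |
| 1.00 | 1.5 / 1.0 / 1.1% | 2.9 / 2.2 / 2.3% | 10% (alpha) |

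On the 26% limb the go probability reaches 80% only at a true HR of 0.74 × exp(−0.8416/7.211) = 0.66. At HR 0.75, 78.6 − 46.1 = 32.5% of trials are significant and still miss 26%.

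**5. Other ways to combine the limbs.** These are simulated at a true rate of 1.25, with the median read from a Kaplan-Meier curve and required to reach 6.5 months (5 × 1.3). Median limb alone 49%; both limbs 35%; either limb 60%.

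**6. A trial that observes exactly its planning assumption.** Observed rate 1.25: z = 7.211 × ln(1.67/1.25) = 2.09, one-sided p about 0.02. The reduction is 1 − 0.7485 = 25.1%, so it fails the 26% limb (1.25 is above 1.236). The exponential median gain is 33%, so it passes the 30% limb (1.25 is below 1.285).

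**7. Where the loss comes from.** A 25% cut-off would give 50% at HR 0.75, against 46% at 26%. The one-point gap costs about 4 percentage points. The rest of the fall from about 79% comes from placing the cut-off at the design effect.

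**The case against.** The strongest reply is that nothing in 11.2 is false. The 80% and 90% are given for statistical significance, they reproduce, and no section claims a probability of a go. A reader might infer that the protocol promises an 80% chance of a go and delivers 46%; the text does not support that. The defect is that the only operating characteristics offered belong to a criterion that the decision does not use.

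A reader might also blame the rule for asking for 26% when the trial assumes 25%. That explains only about 4 points. The median limb is in fact laxer than the design effect (23% against 25%), so the rule as a whole is not simply stricter than the planned effect. Nor can one say without qualification that an active drug is more likely to be dropped than advanced. That holds on the 26% limb, but the go probability is 56% on the 23% equivalent and 60% if either limb is enough.

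Two further replies stand. First, 11.5 calls the rule partly subjective and dependent on toxicity, so every percentage here describes mechanical use. Second, a clinical bar above bare significance is a legitimate choice, the more so because the comparator is itself uncertain: "The estimated historical hazard rate is 1.67 per person-year of follow-up (95% CI: 1.3, 2.14"). The documents therefore do not support insisting that the go cut-off be lowered to 1.40.

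None of this removes the mismatch. The subjectivity clause points to toxicity and does not supply operating characteristics, and a sponsor who sets a higher bar can still say how often the trial will clear it. On every reading examined, the go probability at the planned effect stays well below 80%.

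**Conclusion.** The point holds in this form: the stated power and error rate do not describe the decision that the trial makes. At the planned effect the go probability is about 45% on the 26% limb and about 56% on the 23% equivalent, within a range of roughly 35% to 60% over ways of combining the limbs. At HR 0.70 it is about 64% and 74%; with no effect, about 1% and 2%. In addition, the two limbs of 11.5 contradict each other for observed reductions between 23.1% and 26%, and the planning assumption itself falls in that gap.

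The figures assume exponential survival, a historical rate fixed at 1.67, about 52 deaths, and mechanical use of the rule before toxicity is weighed. The sample size calculation, the estimate of the failure rate and its confidence interval are not affected.

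**What to change.** 1. In 11.5, reconcile the two limbs to a single failure-rate cut-off and give its exponential median equivalent (26% lower failure rate with 35% longer median, or 23% with 30%).
2. In 11.2, state that 80% and 90% are power for one-sided significance only. Add the go rule's own probabilities at HR 0.75, 0.70 and 1.0, for mechanical use before toxicity is considered: about 45%, 64% and 1% if 26% is kept, or about 56%, 74% and 2% if the 23% equivalent is chosen.

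This is wording only. It needs no more patients and no change in conduct. The cost is a less favourable stated chance of success, and it should be done before the survival data are analysed. Moving the go cut-off to the 11.2 critical value (a rate of about 1.40) would bring the go probability back to about 80% and 90%. It would also accept a 16% reduction as enough and raise the false-go rate to 10%. That trade-off is the sponsor's choice and is not required.
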